### Interim analyses and unblinding

The treatment allocation is double-blinded such that trial team members, outcome assessors and patients are unaware of whether a trial patient will receive tranexamic acid or placebo. There are no interim analyses planned. The final analysis of the unblinded results will take place after recruitment is complete, the data have been cleaned and the trial database has been locked as per the procedures detailed in the Data Management Plan (DMP) (version 1.0) and protocol
^18^.

### Data management and integrity

All trial data are managed in accord with the IBMS DMP which is stored in the Trial Master File. The DMP working procedures are produced in conjunction with the London School of Hygiene and Tropical Medicine (LSHTM) policies and procedures, the Clinical Trials Unit and trial specific working procedures, and regulatory requirements. The web database was built to comply with ICH-GCP guidelines and uses MySQL for data storage. Hypertext Preprocessor (PHP) was used to develop the dynamic web pages for the user interface.

Data are collected at each participating site and directly uploaded into the web database. A number of computerised validation checks have been built into the database to ensure all required fields are complete and irregular entries are flagged. In rare cases of poor internet connection or inadequate facilities, paper versions of the Case Report Forms (CRFs) are completed and transcribed into the web database as soon as possible. A delegate cross-checks the transcription between paper and web CRFs and any detected errors are amended on paper and/or web CRFs immediately. Any revisions to a submitted form are saved automatically in a database log with details of who edited the data and when edits were made. Any changes made from the initial form submission are highlighted in each amended version of a form. All other data checks and cleaning are performed by the IBMS lead. This includes using a download report facility within the database to review the data for inconsistencies and resolve queries as per the procedures detailed in the DMP. The final database lock will take place at the end of the trial within three months of the end of data collection. Data will be exported for statistical analysis in Stata Version 15 [StataCorp LP, College Station, Texas, USA].

### Primary outcome

The mean volume of intra-parenchymal bleeding will be compared between trial arms in patients randomised within three hours of injury, adjusting for prognostic covariates.

In the original IMBS protocol
^18^, we said the total volume of intracranial bleeding would be compared between treatment groups. Since publishing the protocol, we have collected blinded data from 1700 trial patients, which suggest that any effect of tranexamic acid on intracranial bleeding expansion may only be reliably detected in intra-parenchymal bleeds. Intra-parenchymal bleeds are less likely to be surgically evacuated compared to subdural and epidural bleeds, which are often larger and therefore substantially increase intracranial pressure and require urgent neurosurgical evacuation. Large subdural and epidural bleeds are easier to evacuate because they occur outside of the brain tissue, whereas intra-parenchymal bleeds often occur deep within the brain tissue so it is difficult to evacuate them without causing further harm. Therefore, we may not be able to reliably examine the effect of tranexamic acid on subdural and epidural bleed expansion given that large bleeds are often evacuated before we can examine any effect of tranexamic acid on them. Including bleeds that may not be affected by tranexamic acid in the primary outcome would dilute any effect of tranexamic acid on intracranial bleeding expansion to the null. Furthermore, when excluding patients who have undergone neurosurgery by the first rated post-randomisation scan, the proportional expansion of intra-parenchymal bleeding from pre- to post-randomisation is greater than for all other types of intracranial bleeding. Indeed, a recent randomised trial found a statistically significant reduction in intracerebral bleeding expansion with tranexamic acid
^24^. Finally, intra-parenchymal bleeds are often spherical in shape, so there is less measurement error with the ABC/2 method of volume estimation compared to subdural and epidural bleeds, which have concave and convex shapes, respectively. For these reasons, the primary outcome will examine the effect of tranexamic acid on the total volume of intra-parenchymal bleeding.

In the original IBMS protocol
^18^, the primary outcome included all patients randomised within 8 hours of injury. Since the protocol was published, an individual patient data meta-analysis was published which included 40,138 patients with acute severe bleeding enrolled in randomised trials of tranexamic acid
^25^. This meta-analysis showed that immediate treatment improved the odds of survival by more than 70% (OR 1·72, 95% CI 1·42–2·10; p<0·0001). Thereafter, the survival benefit decreased by about 10% for every 15 minutes of treatment delay until 3 hours, after which there was no benefit. To quantify any reduction in bleeding volume with tranexamic acid compared to placebo in the IBMS, we must examine the primary outcome during the interval where bleeding is at greatest risk of expansion. If there is a minimal change in bleeding volume after three hours of injury, including patients treated after three hours of injury in the primary analysis will dilute any effect of tranexamic acid towards the null. Therefore, we will restrict the analysis of the primary outcome to three hours of injury.

### Secondary outcomes

(a) Frequency and volume of progressive bleeding in patients randomised within 3 hours of injury: number of patients with a post-randomisation scan with a total bleeding volume of more than 25% of the volume on the pre-randomisation scan;(b) Frequency and volume of new bleeding in patients randomised within 3 hours of injury: number of patients with haemorrhage on the post-randomisation scan that was not seen on the pre-randomisation scan;(c) Number of patients with cerebral infarcts seen on a post-randomisation scan and not known to be present pre-randomisation;(d) Mean volume of intracranial bleeding seen after randomisation in patients who undergo neurosurgical haemorrhage evacuation.(e) Composite poor outcome: progressive bleeding (“a” above), new bleeding (“b” above), cerebral infarction (“c” above), death or the need for neurosurgery within 28 days of injury.

All outcomes for patients treated after three hours of injury will be presented separately.

### Trial status

The first patient was enrolled in the CRASH-3 trial on 20 July 2012. Data collection for the CRASH-3 IBMS started in February 2016. The CRASH-3 trial completed recruitment on 31 January 2019. Routinely collected brain imaging data from patients included in the CRASH-3 IBMS were examined for the purpose of the IBMS and recorded in a web database before this date.

The first and second versions of this SAP were submitted for publication (and publicly available) well before the trials unblinded on 31 May 2019. The reviewer report from peer reviewer 4 was submitted on 6 June 2019. This third version of the SAP is in response to small requests for clarification from peer reviewer 4.

## Statistical analysis plan

### Trial profile

We will show the flow of trial patients in the Consolidated Standards of Reporting Trials (CONSORT) diagram. This will include the total number of patients randomised into the IBMS divided by treatment arm. Each treatment arm will detail the number of patients who received the loading and maintenance doses, the number of patients for whom clinical baseline and outcome data was collected, and the number of patients who were scanned before randomisation and/or after randomisation. We will report the number of patients included in the primary and secondary analyses, the reasons for any post-randomisation exclusions and the number lost to follow-up. If after a patient is randomised into the trial, it is found that they did not meet the eligibility criteria or did not receive their allocated treatment, they are considered to have deviated from the trial protocol. Data from patients who have deviated from the protocol will be included in the intention to treat analysis. If a patient or their representative withdraws consent for data collection, we will use only data up to the point of withdrawal in the analysis.

### Baseline characteristics

We will report baseline characteristics, including, age, sex, GCS, systolic blood pressure, mean number of hours from injury to pre-randomisation scan, mean (and median) haemorrhage volume, different types of haemorrhage (intra-parenchymal, intra-ventricular, subdural, epidural, subarachnoid and petechial), cerebral infarction, oedematous lesions, mass effect findings, and the Marshall classification
^18^. To check that randomisation produced similar groups, we will describe the baseline characteristics of each treatment group with frequencies and percentages.

### Primary analysis

Linear mixed model
^26^ will be used to compare the mean change in intra-parenchymal haemorrhage volume from pre- to post-randomisation between treatment groups. The basic model includes pre- and post-randomisation volumes as correlated outcomes with mean post-randomisation volumes allowed to differ by treatment group but mean pre-randomisation volumes constrained to be the same, and with variances of pre- and post-randomisation volumes allowed to differ. In the absence of missing data, this linear mixed model gives identical estimates of the treatment effect, and near identical standard errors to the more standard ANCOVA analysis. The advantage of the linear mixed model approach is that patients with missing pre- or post-randomisation scans can be included in the analysis, potentially reducing bias and increasing efficiency
^26^.

A linear regression analysis of the blinded data indicated that time from injury to CT scan, GCS, age and systolic blood pressure are significantly predictive of the pre- and post-randomisation bleeding volumes (p<0.05). These covariates and the stratification factor (hospital site)
^27^ will be included in the analysis to improve the precision of the effect estimate. The main effect of site (which is treated as fixed) is accounted for in the model. Because we have relatively few centres (n=14) compared to the number of patients (n= ≈1750), we expect any loss in efficiency from this method (compared to the random centre effects method) to be minimal. The linear mixed model described above will include an interaction between each covariate and whether bleeding volume was measured before and/or after randomisation. This gives treatment effect estimates that are identical to those from the standard ANCOVA model in the absence of missing data. We expect the covariates to affect bleeding volumes in different ways (e.g. older people are likely to have larger bleeds at baseline, more severely unconscious people (low GCS) are likely to have larger bleeds at baseline). In line with the CONSORT guidelines
^28^, we will also report the results from the linear mixed model without covariate adjustment to facilitate synthesis and comparability with other trials that may not include the same covariates.

The blinded data indicates that pre-randomisation and post-randomisation bleeding volumes are positively skewed. Because bleeding volumes are skewed, this data will be log transformed before entered into the linear mixed model. The anti-log of the treatment effect estimate and its corresponding 95% CIs will be presented to aid interpretation. The treatment effect estimates will provide an estimate of the relative increase or decrease in haemorrhage volume with tranexamic acid.

In the original protocol, we planned to analyse the primary outcome using ANCOVA. Since publishing the protocol, we learnt that less than 50% of patients were scanned both pre- and post-randomisation. Because the pre-randomisation mean bleeding volume of the observed data may be different from the true pre-randomisation mean bleeding volume, the estimates from the ANCOVA model may be biased. Compared to ANCOVA, linear mixed models are more powerful and typically less biased when there are missing data
^26^.

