### Trial design and eligibility criteria

The IBMS is a randomised, placebo-controlled, parallel group, international, multi-centre, double-blind trial nested within the CRASH-3 trial. Patients who fulfil the eligibility criteria for the CRASH-3 trial, with a GCS of 12 or less or intracranial bleeding on a CT scan done before randomisation, are eligible for inclusion in the IBMS.

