### Subgroup analyses

*Time from injury to randomisation:* Most intracranial bleeding occurs within hours of injury
^5,
25,
29,
30^. Subgroup analyses will examine whether the effect of tranexamic acid on intracranial haemorrhage is modified by the time from injury to randomisation (≤1 hour, >1 to 3 hours, >3 to 8 hours). If there is minimal haemorrhage expansion after 3 hours
^25^, we expect tranexamic acid will have a lesser effect in reducing haemorrhage expansion in this group compared to the groups treated within 3 hours. We will conduct a linear regression analysis with an interaction between treatment (tranexamic acid, placebo) and time to randomisation (≤1 hour, 1–3 hours, >3–8 hours) to examine whether the effect of tranexamic acid on intracranial haemorrhage volume varies according to the time from injury to randomisation.

There may be an increase in the frequency of cerebral infarction with tranexamic acid in those treated after 3 hours of injury compared to those treated within 3 hours of injury
^15^. We will use relative risks and 95% confidence intervals estimated using generalised linear models to examine whether the effect of tranexamic acid on cerebral infarction varies within subgroups of time from injury to randomisation (≤3 hours, >3 hours). However, given the lower prevalence of cerebral infarction compared to intracranial bleeding, it will be difficult to reliably examine the effect of tranexamic acid on cerebral infarction within time strata. We will examine whether tranexamic acid increases the risk of adverse events in an individual patient data meta-analysis of 15,000 patients with TBI or spontaneous intracerebral haemorrhage (published separately)
^31^.

*Types of haemorrhage*: We will conduct the linear mixed model analysis specified in the primary analysis section separately for subdural, epidural and intra-ventricular bleeds.

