### Missing data from scans not done before or after randomisation

Not all trial patients will be scanned before and after randomisation. We will report the number of patients without scans
^28^ and baseline data for patients included in the analysis to help identify any selective missingness of outcomes by treatment arm
^32^. We will examine whether missing scans are missing equally between treatment arms and appear to be missing completely at random (MCAR). In this case, although missing data reduces the precision of the analysis, it does not bias the treatment effect
^33^.

However, if haemorrhage expansion is associated with the reason the data are missing (patients with haemorrhage expansion may die before the second scan, patients without haemorrhage may not need to be re-scanned), imbalance in missing data by treatment arm can cause bias. We will examine whether the occurrence of missing scans is influenced by fully observed baseline variables (e.g. GCS), using relative risks and 95% confidence intervals estimated using generalised linear models. If they are, and within defined groups data are missing completely at random, the data could be missing at random (MAR)
^33^. For example, if missingness depends on GCS, but within mild, moderate and severe GCS groups missingness is unrelated to haemorrhage or infarction, the data are MAR. In this case, a regression analysis which takes GCS group into account should give unbiased estimates of the treatment effect
^34^.

However, we suspect that within GCS groups, missingness could be related to haemorrhage volume (i.e. low GCS patients are expected to have a greater haemorrhage volume than high GCS patients). In this case, the data would be missing not at random (MNAR) (i.e. even when accounting for the fully observed data, the reason for missing observations still depends on the unseen values)
^33^.

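### The primary analysis takes a plain log of intra-parenchymal volume but gives no rule for the zero volumes the plan itself expects, so observed zeros would be handled as missing

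*SAP article*

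**What the plan says.** The SAP's Primary outcome section defines the comparison: "The mean volume of intra-parenchymal bleeding will be compared between trial arms in patients randomised within three hours of injury". The restriction is on time from injury only. The section Trial design and eligibility criteria admits patients "with a GCS of 12 or less or intracranial bleeding on a CT scan done before randomisation", so neither route into the study requires blood inside the brain tissue.

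The Primary analysis section sets the scale: "Because bleeding volumes are skewed, this data will be log transformed before entered into the linear mixed model". It then interprets the anti-logged coefficient: "The treatment effect estimates will provide an estimate of the relative increase or decrease in haemorrhage volume with tranexamic acid".

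Two other sections show that absent bleeding is expected. Secondary outcome (b) counts the "number of patients with haemorrhage on the post-randomisation scan that was not seen on the pre-randomisation scan". The missing-data section gives as one reason for an absent second scan that "patients without haemorrhage may not need to be re-scanned".

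Under Subgroup analyses the same model is to be run "separately for subdural, epidural and intra-ventricular bleeds".

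No section mentions an added constant, a floor, censoring, a two-part model, or a population limited to patients with an intra-parenchymal bleed.

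**The concern.** The logarithm of zero is undefined, and statistical software returns a missing value. The mixed model was chosen because it tolerates missing readings, so it would run without complaint and treat those zeros as scans that were never done. A zero on the post-randomisation scan is an observed result, and the most favourable one possible. Leaving it out makes the primary comparison depend partly on who still had blood after treatment, which treatment may influence.

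The SAP's missing-data section does not cover this. Its assumption for the primary analysis (missing at random) and its sensitivity analyses concern scans not done, and none of them recovers a rated zero. If the rule is left open, the analyst can drop zeros or add any constant, and those choices can give materially different primary results from the same data.

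**Working it through.** **Step 1: are zeros expected?** Intra-parenchymal bleeding is one of six types listed under Baseline characteristics. A patient who enters with only subdural or epidural blood, or with a GCS of 12 or less and no visible blood, has 0 ml. The SAP's own definition of new bleeding presupposes scans on which blood was absent. Replacing total volume by intra-parenchymal volume can only make zeros more frequent.

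**Step 2: what a plain log does to each patient.**

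| Pre | Post | Result |
|---|---|---|
| >0 | >0 | both readings used |
| >0 | 0 | pre kept; the observed zero is handled as missing at random |
| 0 | >0 | post kept; the known baseline is discarded |
| 0 (or no scan) | 0 (or no scan) | patient contributes nothing |

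The second row is selection on a post-treatment outcome. The third loses the pairing for patients with new bleeding.

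**Step 3: the plan's own figures.** These reproduce.
- Unadjusted: 2 × 28² × (1.96 + 0.84)² / 4² is about 770 per arm, 1540 in total (stated 1542; two-sided 0.05 and 80% power assumed).
- Adjusted: 1542 × (1 − 0.6²) = 986.9 (stated 987).
- Adjusted SD: 28 × √0.64 = 22.4 ml.
- Power at N = 901: Φ(4 / (22.4 × √(4/901)) − 1.96) = Φ(0.72) = 76.4% (stated 76%).

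If 20%, 40% or 60% of the 901 pairs lost a reading, 721, 541 or 360 pairs would remain. The same formula then gives 67%, 55% and 40%. This is only indicative: the inputs are for total volume on the raw scale, and the mixed model still uses single readings.

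**Step 4: when is the ratio biased?** The document gives no share of zeros, so these are scenarios and not estimates.

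*A. Zeros unrelated to treatment.* 20/40/60% of patients have no intra-parenchymal bleed on either scan, in both arms alike; true ratio 24/28 = 0.857. Dropping them returns 0.854 to 0.859. There is no bias.

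*B. Treatment prevents bleeds at random.* Zeros 40% on placebo, 50% on active. Ratio of mean volumes: 0.50/0.60 = 0.83. Ratio among positive volumes: 1.00. The effect is lost.

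*C. Treatment prevents the smallest bleeds.* Same shares; latent log-normal volume with median 10 ml and log SD 1.2.
- Mean log volume above the cut is ln 10 + 1.2 × φ(z)/(1 − p).
- Placebo excess: 1.2 × 0.386/0.60 = 0.773. Active excess: 1.2 × 0.399/0.50 = 0.957.
- Ratio among positives: exp(0.957 − 0.773) = 1.20.
- Ratio of mean volumes: 0.885/0.927 = 0.95 to 0.96.

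Mean volume falls while the log analysis of positives suggests harm.

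*D. Treatment shrinks all bleeds by 0.857, and volumes below a cut read as zero.* Log SD √ln 2 = 0.83, from mean 28 and SD 28 ml. With 20/40/60% zeros and correlations 0.6 to 0.8, positive pairs give ratios of about 0.88 to 0.93. Positive post-only scans give about 0.92 to 0.96. This is attenuation.

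**Step 5: does an added constant solve it?** In C, constants of 1, 0.5, 0.1 and 0.01 ml give 0.80, 0.75, 0.64 and 0.51. With log(volume + 1), A gives 0.89 to 0.94 and D gives 0.75 to 0.78, both against 0.857. In D, constants of 0.5 and 5 ml span 0.71 to 0.855. The answer depends strongly on the constant.

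**The case against.** The strongest reply is that this is an omission and not a declared error. A reader might infer that the plan removes patients according to their outcome. It does not say so: it says only that volumes are logged, and its missing-at-random assumption is written for scans not done. Even under a plain log, the mixed model loses the zero reading and keeps any positive reading from the same patient. That part of the objection stands.

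A reader might also infer that the estimate must move towards no effect, by the amounts in scenario D. The documents do not support that either. Scenario D borrows its spread from total intracranial volume and reaches 20/40/60% zeros only by scoring every bleed below about 9.8, 16.0 or 24.4 ml as zero. Scenario C is also extreme: it abolishes every bleed between about 7.4 ml (exp(ln 10 − 1.2 × 0.253)) and 10 ml. If most zeros belong to patients who never had an intra-parenchymal bleed, scenario A applies and dropping them does no harm.

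New bleeding is analysed separately by relative risk, but for any haemorrhage and not for intra-parenchymal blood alone, so it answers only part of the point.

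The objection does not remove the core. Reading the anti-log as a relative change in volume implies a plain log, because with a constant added it is no longer a ratio of volumes. That stated rule cannot be computed on readings the plan expects. Nor can the gap be left to the protocol: the SAP says that intra-parenchymal volume and the mixed model both replaced what the protocol had planned, so the zero rule belongs here.

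**Conclusion.** The point holds as a defect in the primary analysis rule. The outcome was narrowed without narrowing the population, zeros are expected before and after randomisation, and the prescribed transformation is undefined for them. Applied as written, observed zeros become missing and are handled as missing at random, although they are missing because of their own value.

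Whether the treatment ratio is biased depends on one thing the document does not report: whether treatment changes the chance of a zero on the post-randomisation scan. If it does not, the ratio is unbiased and the loss is of readings. If it does, the result may be attenuated, nullified or reversed. No single figure or direction should be quoted, because the share of zeros is not given and every magnitude above rests on assumed distributions. Confidence is high for the missing rule and low for any particular size of bias.

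**What to change.** State that a rated scan showing no intra-parenchymal blood is an observed 0 ml and is never set to missing. Then choose one of the following.

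(a) Define the log-volume population by a pre-randomisation criterion, namely an intra-parenchymal bleed on the pre-randomisation scan, and treat post-randomisation zeros as left-censored at a stated limit.

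(b) Use a two-part analysis: the relative risk of any post-randomisation intra-parenchymal bleed in all scanned patients, plus the volume ratio among those with a bleed. State that the second part is conditional on having bled.

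Describe the effect measure to match the choice. Keep log(volume + constant) as a sensitivity analysis over several constants, not as the primary model. Apply the same rule to the subdural, epidural and intra-ventricular models, and to the post-neurosurgery volumes if the log is carried over there. Report the number of zeros by arm and scan.

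The Trial status section dates unblinding to 31 May 2019 and places this version after it. The rule should therefore be dated, with a statement of whether it was set before volumes by arm were seen.

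The cost is a few sentences and a few extra model runs. Option (a) needs a stated rule for patients without a pre-randomisation scan and gives up some of the mixed model's advantage in using them. Option (b) gives two results in place of one, so the SAP must say which is primary.
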